**Fig. 1 Fig1:**
[figure not shown]
*Flow chart* showing the process of participant recruitment, treatment, and analysis

**Fig. 2 Fig2:**
[figure not shown]
SPIRIT figure of enrolment, interventions, and assessments. EA electroacupuncture, UC usual care, VAS visual analogue scale, ODI Oswestry Disability Index, EQ-5D EuroQol five-dimensional questionnaire

### Participants

(Same as or similar to the pilot protocol [26].)

#### Inclusion criteria

Participants aged 19–70 yearsParticipants with LBP that has persisted or recurred after back surgery, regardless of leg pain, with the current pain episode continuing for three weeks or longerParticipants with a pain score on the VAS ≥ 50 mmParticipants who have voluntarily agreed to participate in the study and have provided written informed consent

#### Exclusion criteria

Participants diagnosed with a serious disease(s) that may potentially cause LBP (e.g. spinal infection, cancer, or inflammatory spondylitis)Participants with severe neurological symptoms or progressive neurological deficits (e.g. bowel/bladder symptoms, paraplegia, or presence of neurogenic claudication)Participants whose cause of pain is not the result of spine or soft tissue disease(s) (e.g. cancer, fibromyalgia, gout, or rheumatoid arthritis)Participants with a chronic disease(s) that may potentially influence treatment effects or treatment result analyses (e.g. diabetic neuropathy, dementia, severe cardiovascular disease, or epilepsy)Participants for whom acupuncture may potentially be unsafe or inappropriate (e.g. those with severe cardiovascular disease, hemorrhagic disease, anticoagulant therapy history, or severe diabetes at high risk of infection)Participants who are currently pregnant or planning to be pregnantParticipants with a psychiatric disease(s) or who are currently receiving treatment for a psychiatric disease(s)Participants currently participating in other clinical trial(s)

### Randomization and allocation concealment

Participants will be randomly allocated to either the EA plus UC group or the UC alone group with equal probability. Computer-generated block randomization will be used to ensure that both groups are assigned the same number of participants at a 1:1 ratio. A center-stratified block randomization scheme will be developed and administered by a statistical expert at the Korea Institute of Oriental Medicine using SAS® Version 9.4 (SAS institute Inc., Cary, NC, USA).

Sequentially numbered, sealed opaque envelopes of the same shape and size will be used to conceal group allocation and avoid selection bias at each recruitment site. Patients will be assigned to one of the two groups according to the randomization code and practitioners will deliver the allocation-appropriate treatment. Each trial participation site will store the randomization numbers in a double-locked cabinet on the hospital grounds. The allocation sequence will be concealed from the outcome assessor to prevent detection bias.

### Blinding

As the practitioners and participants in this trial cannot be blinded to the allocation of treatment groups due to the differences in the nature of the EA intervention, only the outcome assessor will be blinded. Outcome assessors will not participate in the EA or UC treatment, and they will conduct the outcome assessments in a separate room without any knowledge of participant allocation and are therefore considered safe from detection bias [32]. Unblinding the assessors will be permissible only in specific situations, such as when knowledge of the actual treatment is highly necessary for the appropriate management of participants (e.g. serious AEs (SAEs).

### Education on standardization of study procedures

First, we will develop standard operating procedures (SOPs) for the entire trial, interventions, roles, and training of assessors, researchers, and CRCs through a consensus based on experience with the previous pilot trial [26]. All researchers will be required to complete a clinical trial training in accordance with their individual roles. Licensed KMDs will be involved in this trial as practitioners or outcome assessors. Specifically, practitioners will have had three or more years of clinical experience after being certified with KMD licensure by the Korean Ministry of Health and Welfare. They will have undergone an educational course to standardize the study procedures and this process will ensure that they adhere to the study protocol and are familiar with the study interventions and their administration. All of the practitioners involved in the trial will undergo intensive training customized by role (two training sessions of a 1-h duration or more, with each session including lectures and hands-on sessions) to enable full comprehension of the EA procedure, which is semi-standardized regarding acupoints, needling depth, and manual stimulation methods. The study details, protocol, and outcome assessment process will additionally be standardized among outcome assessors through trainings based on the SOPs.

In this study, to improve the adherence to protocol, the researchers will be trained on the SOPs and regularly monitored. The participants will be thoroughly explained on the process of the study, noticed of their visit schedules via phone calls or text messages, and provided financial compensation to ensure their adherence to the protocol.

### Interventions

#### EA with UC group

In the EA with UC group, both acupuncture and EA will be performed. The intervention will be administered by KMDs using 0.25-mm diameter × 40-mm length disposable stainless steel needles (Dongbang Acupuncture Inc., South Korea) and will be provided a total of eight sessions (two sessions/week) for a period of four weeks. Semi-standardized acupuncture points will be used. In other words, Jia-ji (six acupoints, bilateral Ex-B2 at L3, L4, and L5) will be used as the required and standardized points; a maximum of nine acupuncture points will be used as additional points. These additional points will be selected depending on the patients’ symptoms. Electrical stimulation will be applied to four acupuncture points of Jia-ji (bilateral Ex-B2 at L3 and L5) and performed for 15 min with a biphasic waveform current, which utilizes alternating interrupted waves and continuous waves at 50 Hz in a triangular form and a compressional wave [33] using an electronic stimulator (Fig. 3, ES-160, ITO Co. Ltd., Tokyo, Japan). The procedure for EA treatment will be designed to reflect actual clinical settings and will be based on consensus among 21 acupuncture and spinal disorder experts in several offline meetings to ensure the feasibility of the study design.

**Fig. 3 Fig3:**
[figure not shown]
Electrical machine (ES-160, ITO Co. Ltd., Tokyo, Japan)

All participants will receive the same UC treatment (see below for details) for the same four-week period. Each intervention will be provided in 5- to 10-min intervals. More detailed procedures according to the STRICTA are attached in Additional file 1.

#### UC group

The UC for LBP generally consists of conventional drugs for LBP (pain medication with muscle relaxants), physical therapy, and an educational program based on LBP clinical guidelines [30]. Conventional pharmaceutical or non-pharmaceutical treatments excluding invasive interventions (e.g. analgesics and physical therapy are allowed; injections and surgery are disallowed) relevant to post-surgical LBP will be administered and monitored carefully at each visit. Physical therapy will be administered by practitioners twice a week during the treatment period (four weeks). Interferential current therapy (ICT; EF-150, OG Giken Co., Okayama, Japan; STI-300, Stratek Co. Ltd., Anyang, South Korea) and superficial heat therapy will be applied for 15 min each. These physical therapies were selected with reference to the most common treatments used in LBP patients as assessed from the 2011 Korean HIRA statistics [29] or clinical practice guidelines [30]. Participants will receive a standardized educational program on LBP, comprising a 20-min video and a brochure, which includes information on the post-surgical pain prevalence, pathophysiology, and management tips for preventing LBP while performing everyday activities through exercise, such as cat and camel, single knee to chest, and bridging exercise.

This confirmatory, multi-center, pragmatic RCT is designed to investigate the effectiveness, as opposed to the efficacy, of EA combined with UC compared to UC alone in patients with non-acute pain following back surgery. Therefore, neither a placebo nor sham EA will be employed as an active control [34]; additionally, this trial aims to assess the effectiveness, safety, and cost-effectiveness under settings reflecting real-world conditions.

### Outcome measurements

#### Primary outcome

The primary outcome of this study is the pain intensity of LBP after back surgery as assessed by a VAS. Post-surgical LBP severity will be quantified using a VAS pain intensity score as determined on a 100-mm horizontal line, where 0 indicates no pain and 100 indicates intolerable pain [35, 36]. The level of back pain during the previous week will be assessed using a 100-mm pain VAS at baseline (visit 2), before each treatment session (visits 2–9), and at each post-treatment follow-up visit (visits 10–12); the primary endpoint will be VAS pain intensity score at visit 10, representing treatment completion. The outcome measures will be assessed before treatment at each visit to ascertain the effectiveness of the previous treatment(s).

#### Secondary outcome

Regarding secondary outcomes, the Oswestry Disability Index (ODI) will be used to assess disability associated with back pain [37] and the EuroQol 5-Dimension (EQ-5D) scale [38] will be employed for health-related quality of life.

The ODI consists of ten questions pertaining to daily activities and covers the following: experiencing general pain, practicing self-care (e.g. washing, dressing), lifting objects, sitting, standing, walking, sleeping, travelling, engaging in sexual activity if applicable, and participating in social activities. The items are rated on 6-point scales scored in the range of 0–5, with higher scores indicating higher pain-associated disability. The participants will be asked to complete the validated Korean version [39] of the ODI before treatment on the second and sixth visits and at each post-treatment follow-up (visits 10–12).

The validated Korean version of the EQ-5D [40] will be used to assess health-related quality of life in post-surgical LBP patients. The EQ-5D consists of five dimensions: usual activities; mobility; pain/discomfort; anxiety/depression; and self-care. The scales for these dimensions are in the range of 1–3 and lower scores represent a better health status. The EQ-5D scores will be evaluated before treatment at the initial treatment session (second visit) and at each follow-up (visits 10–13). For cost-effectiveness analysis, EQ-5D will be additionally evaluated via telephone at the 13th visit.

Changes in medicine intake and dosage will be investigated through interviews at each visit. Additional pain-related treatments will be allowed and the type and frequency will be recorded as part of the feasibility design (e.g. physiotherapy, medication).

### Adverse events

Any AEs will be monitored and reported by the researchers at each visit. All expected and unexpected AEs potentially related to the study will be monitored and their progress will be recorded until resolved. The physicians will decide whether trial participation should be discontinued based on these reports.

### Sample size

An appropriately powered full-scale sample size has been estimated using the mean between-group difference in the primary endpoint (VAS pain intensity score for LBP) identified in the previous pilot study. Based on intention-to-treat (ITT) analysis, the mean difference and standard deviation (SD) in the VAS pain intensity score for LBP between the EA plus UC group and UC alone group is estimated to be 14.02 mm ± 22.12 mm. Although this reduction in pain intensity is not moderately clinically meaningful, it does represent a minimally important difference [41].

The total number of individuals required per group is 40, considering a two-tailed test with 80% test power and a 5% significance level. After accounting for a 25% drop-out rate and the 1:1 allocation ratio, the final sample size per group has been calculated to be 54, resulting in a total sample size estimate of 108 for a full power analysis.

### Statistical analysis

The statistical analysis will be conducted using both the ITT and per-protocol (PP) analysis principles in parallel. Multiple imputation methods will be used for missing data in the ITT analysis. A PP analysis will be performed as a secondary analysis excluding data from drop-outs for any reason. An interim analysis will not be performed. An independent t-test or Wilcoxon rank sum test will be used to analyze continuous data to test for significance in between-group differences and will be presented as the mean ± SD. Chi-square test or Fisher’s exact test will be conducted for categorical data and the data will be described as the frequency and percentage (%). To analyze the VAS pain intensity score as the primary outcome, we will perform an analysis of covariance (ANCOVA) considering the baseline scores as covariates and treatment group as the fixed factor. A paired t-test or Wilcoxon signed rank test will be performed to analyze within-group differences pre and post treatment. Repeated measure analysis of variance (RMANOVA) will be used to analyze the between-group differences at each visit. Subgroup analysis will be conducted according to age, gender, and medical history (e.g. the existence of osteoporosis, pre-surgery diagnoses), which may have the possibility of affecting the treatment effects on each outcome.

A safety assessment will be performed for all AEs occurring during the study period. The incidence of AEs, AEs leading to withdrawal, and SAEs will be summarized by group and analyzed using Fisher’s exact test or chi-square test.

All statistical analyses will be conducted by a designated statistician blinded to group allocation with SAS® Version 9.4 (SAS institute Inc., Cary, NC, USA) for Windows. The level of significance will be set at 5%.

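### ODI and EQ-5D appear to get no baseline-adjusted comparison although both are measured before treatment; extending the VAS ANCOVA would gain precision at no cost

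*Protocol article*

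**What the plan says.** All statements are in the protocol article.

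- **General rule** (Statistical analysis): "An independent t-test or Wilcoxon rank sum test will be used to analyze continuous data to test for significance in between-group differences". No covariate is named, and the text does not say whether follow-up scores or changes are compared.
- **VAS only** (Statistical analysis): "To analyze the VAS pain intensity score as the primary outcome, we will perform an analysis of covariance (ANCOVA", with the model described as "considering the baseline scores as covariates and treatment group as the fixed factor".
- **Repeated measures** (Statistical analysis): "Repeated measure analysis of variance (RMANOVA) will be used to analyze the between-group differences at each visit". No outcome and no baseline covariate is named.
- **Secondary outcomes** (Secondary outcome): "Regarding secondary outcomes, the Oswestry Disability Index (ODI) will be used to assess disability associated with back pain", and EQ-5D is used for quality of life.
- **Baselines are collected** (Secondary outcome): participants complete the Korean version "of the ODI before treatment on the second and sixth visits and at each post-treatment follow-up". For quality of life, "The EQ-5D scores will be evaluated before treatment at the initial treatment session (second visit".

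**The concern.** The plan accepts baseline adjustment for pain and gives no reason to withhold it from function and quality of life. Functional improvement is named next to pain control in the aim. Because the ANCOVA is tied expressly to the VAS, the generic sentence on continuous data is the only between-group test of ODI and EQ-5D at a given time point that the article clearly offers.

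Randomization is stratified by center alone, so nothing in the design balances baseline ODI or EQ-5D. In a trial of this size, part of any chance difference at visit 2 would remain in an unadjusted comparison, and its confidence interval would be wider than the collected data allow.

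**Working it through.** **1. The plan's own sample size.** Under Sample size, the VAS difference "is estimated to be 14.02 mm ± 22.12 mm", with two-sided 5% significance and 80% power. By the normal approximation, n per arm = 2 × [22.12 × (1.960 + 0.842) / 14.02]² = 39.08, rounded up to 40. With 25% drop-out, 40 / 0.75 = 53.3, rounded up to 54. Both stated figures reproduce and are not in question. They give the range used below: 40 evaluable to 54 randomized per arm.

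**2. Assumption.** Let r be the correlation between the visit-2 score and the follow-up score. The documents do not give it, so r = 0.3 to 0.6 is assumed. The change-score formulas also assume equal SDs at the two times.

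**3. Precision.** In units of the outcome variance, a follow-up score has variance 1, a change score 2(1 − r), and the ANCOVA residual 1 − r².

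| | r = 0.3 | r = 0.5 | r = 0.6 |
|---|---|---|---|
| ANCOVA / follow-up score, 1 − r² | 0.91 | 0.75 | 0.64 |
| ANCOVA / change score, (1 + r)/2 | 0.65 | 0.75 | 0.80 |
| CI width against follow-up score, √(1 − r²) | 0.95 | 0.87 | 0.80 |
| Equivalent n per arm, 40/(1 − r²) | 44.0 | 53.3 | 62.5 |
| Power for an illustrative 0.5 SD effect, 40 per arm (61% unadjusted) | 65% | 73% | 80% |

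ANCOVA is the more precise whichever score the t-test uses.

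**4. Chance imbalance.** The baseline difference between arms has SD √(2/n) in baseline SD units.

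- n = 40: SD 0.22, 95% range ±0.44; it exceeds 0.25 SD in 26% of trials.
- n = 54: SD 0.19, 95% range ±0.38; it exceeds 0.25 SD in 19% of trials.

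A fraction r of the imbalance carries into a follow-up-score comparison, and −(1 − r) into a change-score comparison. At the 95% limit for n = 40 (0.438 SD):

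- Follow-up score: 0.3 × 0.438 = 0.13 SD to 0.6 × 0.438 = 0.26 SD.
- Change score: −0.7 × 0.438 = −0.31 SD to −0.4 × 0.438 = −0.18 SD.

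**5. What this does to the test.** Given an imbalance of k standard errors, the follow-up-score test statistic under no effect is distributed as N(rk, 1 − r²). At k = 1.96 the chance of a false positive is about 8% for r = 0.3 and 13% for r = 0.5. At k = 1 it is about 5% for both. Averaged over all randomizations it is 5%.

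**The case against.** **The quoted sentence does not name ODI or EQ-5D.** It speaks of continuous data in general and could also cover baseline characteristics. This stands as a limit: applying it to these outcomes is an inference, though the natural one, since ANCOVA is reserved for the VAS.

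**The repeated-measures ANOVA is not restricted to the VAS.** ODI (visits 2, 6 and 10–12) and EQ-5D (visits 2 and 10–13) both fit it. If visit 2 enters as a response, the group-by-time contrast of visit 2 with visit 10 is a comparison of change, which does use the baseline. So it cannot be said that a two-sample test is the whole plan. But the article does not say that visit 2 enters. Even if it does, that contrast is a change-score comparison, against which ANCOVA still saves 35% to 20% of the variance. The generalized linear model under Cost-effectiveness analysis serves the cost-effectiveness ratio and does not name baseline utility.

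**Secondary models are often left to the analysis plan.** The missing rule for choosing between t-test and Wilcoxon is such a detail and is not pressed here. The general test is different: the article states it, and a better one is available from the same data.

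**Stronger readings a reader might infer.**

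- That the secondary comparisons are biased or have inflated error. They are not: under randomization the unadjusted test is unbiased with 5% type I error overall.
- That baseline imbalance passes whole into the comparison. Only the fractions in the working do.
- That a Wilcoxon test contradicts presentation as mean ± SD. Those are descriptive summaries, and a rank test is defensible for EQ-5D items scored 1 to 3.

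**Conclusion.** The point holds as a free improvement to secondary analyses, not as an error of validity. As written, the article gives no clearly baseline-adjusted comparison of ODI or EQ-5D, although the visit-2 scores exist.

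The size depends on an assumed r of 0.3 to 0.6. Against follow-up scores the variance falls by 9% to 36%, from a modest 4 extra participants per arm up to about 22. Against change scores it falls by 35% to 20%. For EQ-5D, with its coarse item scores, the linear variance formula is only approximate.

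The primary VAS analysis is already baseline-adjusted, and neither it nor the sample size is affected.

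**What to change.** State that the VAS ANCOVA extends to ODI and EQ-5D at visit 10 and at the later follow-ups, with treatment group as factor and each outcome's own visit-2 score as covariate. Report the adjusted mean difference with its 95% confidence interval. Keep any rank-based test as a named sensitivity analysis rather than an alternative to the main test. Say which outcomes the repeated-measures ANOVA covers and whether visit 2 enters as a response, as a covariate or not at all.

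Center may be added as a further term because randomization is stratified by center. That would be an addition, since the stated primary model has only baseline and treatment group, and the fix does not depend on it.

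The cost is a change of analysis wording. No new data, visits or participants are needed.

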### Design

This study is a multi-center, randomized, assessor-blinded trial with two parallel arms and an active control. This study will be conducted in three hospitals in South Korea. Participants will be independently recruited at each hospital site through online advertisements placed on the hospital website and offline on-site advertisements, such as hospital bulletin boards, to obtain the appropriate participant enrollment and target sample size. Potential participants will be required to undergo screening to determine their eligibility. When eligible, participants will be asked to provide written informed consent, after which the baseline evaluation will be conducted by a study researcher. At screening, a clinical research coordinator (CRC) will collect information on various basic sociodemographic characteristics such as gender, age, vital signs, height, weight, and medication history. Korean medicine doctors (KMDs) will collect information on the medical history of individuals who have received spinal surgery, such as the timing of surgery, type of surgery (i.e. fusion, decompression, or discectomy), surgically involved vertebra(e), number of surgeries, time of pain, onset of symptoms, and duration of symptoms. On their second visit, screened participants who are considered eligible for trial participation based on the inclusion and exclusion criteria will be randomly allocated using a 1:1 ratio to either the EA plus UC group or the UC alone group. After randomization, the treatment procedure will be scheduled and managed by a CRC. To maximize participant retention, there will be flexibility during the visit period and researchers will allow actual visits to be within seven days of prescheduled visits. The post-treatment follow-up will occur one, four, and eight weeks following the four-week interventional period to know whether the treatments effects are maintained.

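### The primary ANCOVA omits center although randomization is stratified by center; if center predicts visit-10 VAS after baseline, the standard error is somewhat too large, and adding the term costs almost nothing

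*Protocol article*

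**What the plan says.** All sections are in the protocol article.

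- Design: "This study will be conducted in three hospitals in South Korea". Each hospital recruits independently.
- Randomization and allocation concealment: "A center-stratified block randomization scheme will be developed and administered by a statistical expert".
- Primary outcome: "the primary endpoint will be VAS pain intensity score at visit 10, representing treatment completion".
- Statistical analysis, for the primary outcome: "we will perform an analysis of covariance (ANCOVA) considering the baseline scores as covariates and treatment group as the fixed factor".

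The model therefore has one covariate and one factor, and center is neither. The Statistical analysis section does not bring center into the repeated-measures analysis or the subgroup list either. Study limitations discusses only factors that were not used for stratification (age, gender, medical history), so it gives no reason for leaving center out.

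**The concern.** The analysis should reflect the restrictions placed on the randomization. Blocking within hospital makes the arms nearly equal in size at each site, so a hospital whose patients score higher on average raises both arm means alike. The actual sampling spread of the treatment estimate then excludes most of the variation between hospitals. A model without center does not recognize this and keeps that variation in its residual variance.

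If hospitals differ in visit-10 VAS after baseline adjustment, the reported standard error exceeds the true one, the confidence interval is wider than it need be, and the test rejects less often than its nominal level. What is at stake is efficiency and an accurate standard error for the main result.

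**Working it through.** **Inputs from the document (Sample size section).** Difference and SD: "is estimated to be 14.02 mm ± 22.12 mm". Error rates: "considering a two-tailed test with 80% test power and a 5% significance level". Evaluable patients: "The total number of individuals required per group is 40". Inflation: "After accounting for a 25% drop-out rate and the 1:1 allocation ratio".

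**Assumption.** c is the share of visit-10 VAS variance, after baseline adjustment, that lies between centers. The document gives no value, so a range of 0 to 0.15 is shown.

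**Step 1. Reproduce the plan's figure.** n per arm = 2 × [22.12 × (1.960 + 0.842) / 14.02]² = 39.08, rounded up to 40. Then 40 / (1 − 0.25) = 53.3, rounded up to 54, or 108 in total. The stated figures reproduce. This calculation takes no credit for baseline or center.

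**Step 2. Planned standard error.** 22.12 × √(2/40) = 4.946 mm, so the expected z is 14.02 / 4.946 = 2.8345. Power by the normal approximation is Φ(2.8345 − 1.960) = 80.9% (79.9% by the noncentral t).

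**Step 3. Effect of omitting center, with balance within center.** The model without center reports 4.946, while the true spread is 4.946 × √(1−c). Hence:

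- ratio of reported to true standard error = 1/√(1−c)
- true two-sided error = 2 × [1 − Φ(1.960/√(1−c))]
- power without center = Φ[(2.8345 − 1.960)/√(1−c)]
- power with center = Φ[2.8345/√(1−c) − 1.960]

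| c (assumed) | SE ratio | True two-sided error | Power without center | Power with center | Gap (points) |
|---|---|---|---|---|---|
| 0 | 1.000 | 5.0% | 80.91% | 80.91% | 0 |
| 0.02 | 1.010 | 4.8% | 81.15% | 81.68% | 0.5 |
| 0.10 | 1.054 | 3.9% | 82.17% | 84.80% | 2.6 |
| 0.15 | 1.085 | 3.4% | 82.86% | 86.75% | 3.9 |

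**Step 4. Simulation check.** Settings were three centers, 40 per arm, stratified blocks of 4 (an assumption, since the article gives no block size) and 10,000 runs per setting. At c = 0.10 the model without center reports a mean standard error of 4.96 against an actual spread of 4.72; with center the two agree (4.71 and 4.72). Type I error is 4.0% without center and 4.8% with it. Power is 80.3% and 83.4%. At c = 0 power is 79.7% without center and 79.4% with it, so the extra term costs next to nothing.

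**Step 5. Drop-out.** If 25% are lost at random and observed cases are analyzed, balance within center is only partly kept. The true variance of the unadjusted estimate is then proportional to (1−c) + 0.25c = 1 − 0.75c, and the overstatement falls to 1/√(1−0.75c):

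- c = 0.10: 1/√0.925 = 1.040, or 4.0% instead of 5.4%
- c = 0.15: 1/√0.8875 = 1.061, or about 6% instead of 8.5%

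This trims the overstatement but does not close the power gap. At c = 0.10, power without center is Φ(0.8745 × 1.040) = 81.8%, against about 84.8% with it. Multiple imputation, which the article plans for the intention-to-treat analysis, was not modeled.

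**The case against.** The strongest case against the point has four parts.

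1. **The loss is conditional.** The documents give no center variance, and with no center effect the two models perform alike. Common procedures and training across sites may keep the effect small. This stands, and the point is worded accordingly. Baseline adjustment also absorbs center differences in initial severity, so only what remains after baseline counts.

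2. **Nothing promised is broken.** A reader might infer that the trial is underpowered, that its type I error is wrong in the harmful direction, or that the estimate is biased. The documents support none of these. The sample size used the unadjusted SD and reproduces, power without center is not below the planned level at any c in the table, and the true error rate is at or below 5%. Randomization protects the estimate whether or not center is in the model.

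3. **The benefit of stratifying is not wasted.** A reader might infer that it is. In fact the true spread of the estimate shrinks whichever model is fitted (4.72 at c = 0.10 in the simulation), and power without center still rises from 81.2% to 82.9% as c goes from 0.02 to 0.15. What is missing is full credit for that precision in the reported standard error.

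4. **A fuller model may sit in the analysis plan, which is not shown.** This carries little weight for the primary model, because the article names its terms instead of deferring them. It does carry weight for the imputation model and the secondary-outcome models, whose terms the article leaves open; they are not part of this point.

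**Conclusion.** The mismatch is in the text: allocation is stratified by center, and the stated primary model has no center term. Its direction is certain wherever center matters, namely a standard error that is too large and a conservative test. Its size is not known from the documents. Under an assumed residual center share of 2% to 15%, the overstatement is at most about 1% to 8.5% and the cost is roughly 0.5 to 4 points of power relative to the center-adjusted model. These figures rest on the stated difference and SD, 40 analyzed per arm, a normal approximation and near-complete balance within center. This is an improvement in efficiency of minor to moderate weight, not a threat to the validity of the trial.

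**What to change.** In the Statistical analysis section, and in the analysis plan, specify the primary model before any unblinded analysis as: visit-10 VAS = treatment + baseline VAS + center, with center as a fixed factor with three levels.

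The cost is 2 degrees of freedom: residual df falls from 80 − 3 = 77 to 75 with 80 patients analyzed, or from 108 − 3 = 105 to 103 with all 108. Center is known for every participant from the randomization, so no new data are needed, and the sample size stays at 108.
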